## 8. ADMINISTRATIVE MATTERS

The trial will be carried out in compliance with the protocol, the principles laid down in the Declaration of Helsinki, in accordance with the ICH Harmonised Tripartite Guideline for Good Clinical Practice (GCP) and in accordance with applicable regulatory requirements.

### 8.1 ETHICS

#### 8.1.1 Institutional Review Board or Independent Ethics Committee

The trial will not be initiated before the protocol and informed consent and subject information form have been reviewed and received approval / favourable opinion from the local Institutional Review Board (IRB) or an Independent Ethics Committee (IEC). Should a protocol amendment be made that needs IRB / IEC approval, the changes in the protocol will not be instituted until the amendment and revised informed consent (if appropriate) has been reviewed and received approval / favourable opinion from the local IRB or IEC. A protocol amendment intended to eliminate an apparent immediate hazard to subjects may be implemented immediately providing that the appropriate regulatory authorities and IRB / EC are notified as soon as possible and an approval is requested. Protocol amendments only for logistical or administrative changes may be implemented immediately; the IRB / IEC need to be informed only.

The constitution of the IRB or IEC must meet the requirements of the regulatory agencies. A list of the IRB / IEC members, with names and qualifications, will be requested. If such a list is unavailable, the investigator must provide the name and address of the IRB/IEC along with a statement from the IRB/IEC that it is organised according to GCP and the applicable laws and regulations. The IRB or IEC must also perform all duties outlined by the requirements of the regulatory agencies.

#### 8.1.2 Informed Consent and Subject Information

Prior to subject participation in the trial, written informed consent will be obtained from each subject according to the regulatory and legal requirements of the participating country. Each signature must be dated by each signatory and the

|                                                         |                                                 |                                                           |
|---------------------------------------------------------|-------------------------------------------------|-----------------------------------------------------------|
| Prepared by:
[name]
Date: 22.06.2010 | Approved by:
[name]
Date:22.06.2010 | Protocol No. ZYH1.09.003.01 .PROT
Version No.: 1.0 (R) |
|---------------------------------------------------------|-------------------------------------------------|-----------------------------------------------------------|

|                                                                                  |                                                                                           |              |
|----------------------------------------------------------------------------------|-------------------------------------------------------------------------------------------|--------------|
| [figure not shown] | Clinical trial Protocol for ZYH1 – Phase II
ZYH1.09.003.01.PROT

DCGI Submission | Confidential |
|----------------------------------------------------------------------------------|-------------------------------------------------------------------------------------------|--------------|

informed consent and any additional subject information form retained by the investigator as part of the study records. A signed copy of the informed consent and any additional subject information must be given to each subject or the subject's legally authorised representative.

The subject must be informed that his / her medical records may be examined by authorised monitors or Clinical Quality Assurance auditors appointed by Cadila Healthcare Limited, by appropriate IEC / IRB members and by inspectors from regulatory authorities.

Should a protocol amendment be made, the subject consent form and subject information form may need to be revised to reflect the changes to the protocol. It is the responsibility of the investigator to ensure that an amended consent form is reviewed and received approval / favourable opinion from the IRB or IEC, and that it is signed by all subjects subsequently entered in the trial and those currently in the trial, if affected by the amendment.

## 8.2 RECORDS

### 8.2.1 Drug Accountability

Drug supplies, which will be provided by the sponsor, must be kept in a secure, limited access storage area under the storage conditions defined by the sponsor. If necessary, a temperature log must be maintained to make certain that the drug supplies are stored at the correct temperature.

The investigator and/or pharmacist must maintain records of the product's delivery to the trial site, the inventory at the site, the use by each subject, and the return to the sponsor or alternative disposition of unused product(s). These records will include dates, quantities, batch/serial numbers, expiration dates (if applicable), and the unique code numbers assigned to the investigational product(s) and trial subjects. Investigators will maintain records that document adequately that the subjects were provided the doses specified by the protocol and reconcile all investigational product(s) received from the sponsor. At the time of return to the sponsor, the investigator must verify that all unused or partially used drug supplies have been returned by the clinical trial subject and that no remaining supplies are in the investigator's possession.

|                                                         |                                                 |                                                           |
|---------------------------------------------------------|-------------------------------------------------|-----------------------------------------------------------|
| Prepared by:
[name]
Date: 22.06.2010 | Approved by:
[name]
Date:22.06.2010 | Protocol No. ZYH1.09.003.01 .PROT
Version No.: 1.0 (R) |
|---------------------------------------------------------|-------------------------------------------------|-----------------------------------------------------------|

|                                                                                  |                                                                                           |              |
|----------------------------------------------------------------------------------|-------------------------------------------------------------------------------------------|--------------|
| [figure not shown] | Clinical trial Protocol for ZYH1 – Phase II
ZYH1.09.003.01.PROT

DCGI Submission | Confidential |
|----------------------------------------------------------------------------------|-------------------------------------------------------------------------------------------|--------------|

## 8.2.2 Emergency code break

This will not be applicable as the study is an open-label study.

## 8.2.3 Case Report Forms

Case report forms for individual subjects will be provided by the sponsor. A copy remains with the investigator as a permanent record, and the original will be returned to the sponsor.

Case report forms are used to record clinical trial data and are an integral part of the trial and subsequent reports. The case report forms, therefore, must be legible and complete. All forms must be filled in using a black ballpoint pen. Errors must be lined out but not obliterated and the correction inserted, initialled and dated.

The investigator must sign a declaration ensuring accuracy of data recorded in the case report forms.

Case reports forms must be kept current to reflect subject status at each phase during the course of trial. Subjects are not to be identified on the case report form by name. Appropriate coded identification (e.g. Subject Number) and subject initials must be used. The investigator must make a separate confidential record of these details (subject identification code list) to permit identification of all subjects enrolled in a clinical trial in case follow-up is required.

Relevant medical history prior to enrolment will be documented at the baseline visit. Thereafter during the trial narrative statements relative to the subject's progress during the trial will be maintained. See also 8.2.4.

The investigator will be responsible for retaining all records pertaining to the trial as specified in the agreement.

## 8.2.4 Source documents

Source documents provide evidence for the existence of the subject and substantiate the integrity of the data collected. Source documents are filed at the investigator's site. Data reported on the Case Report Forms that are derived from source

|                                                         |                                                 |                                                           |
|---------------------------------------------------------|-------------------------------------------------|-----------------------------------------------------------|
| Prepared by:
[name]
Date: 22.06.2010 | Approved by:
[name]
Date:22.06.2010 | Protocol No. ZYH1.09.003.01 .PROT
Version No.: 1.0 (R) |
|---------------------------------------------------------|-------------------------------------------------|-----------------------------------------------------------|

|                                                                                  |                                                                                           |              |
|----------------------------------------------------------------------------------|-------------------------------------------------------------------------------------------|--------------|
| [figure not shown] | Clinical trial Protocol for ZYH1 – Phase II
ZYH1.09.003.01.PROT

DCGI Submission | Confidential |
|----------------------------------------------------------------------------------|-------------------------------------------------------------------------------------------|--------------|

documents must be consistent with the source documents or the discrepancies must be explained.

The investigator may need to request previous medical records or transfer records, depending on the trial; also current medical records – not just shadow charts – must be available.

The following data to be reported on the CRF should be included and derived from the source documents:

- Subject identification (initials, gender, data of birth/age)
- Subject participation in the trial (substance, trial number, subject number, date informed consent given)
- Dates of subject's visits
- Medical history
- Medication history
- Adverse events (AE onset and end)
- Serious adverse events (SAE onset and end)
- Originals or copies of laboratory results
- Originals or copies of X-rays and Ultrasound findings, ECG results, EEG results, neurological findings, endoscopy findings and other results based on hard copies of medical machinery, etc., if applicable.
- Conclusion of subject's participation in the trial.

#### **8.2.5 Direct access to source data / documents**

The investigator / institution will permit trial related monitoring, audits, IRB / IEC review and regulatory inspection, providing direct access to all related source data / documents. Case report forms and all source documents, including progress notes and copies of laboratory and medical test results must be available at all times for

|                                                         |                                                 |                                                           |
|---------------------------------------------------------|-------------------------------------------------|-----------------------------------------------------------|
| Prepared by:
[name]
Date: 22.06.2010 | Approved by:
[name]
Date:22.06.2010 | Protocol No. ZYH1.09.003.01 .PROT
Version No.: 1.0 (R) |
|---------------------------------------------------------|-------------------------------------------------|-----------------------------------------------------------|

|                                                                                  |                                                                                           |              |
|----------------------------------------------------------------------------------|-------------------------------------------------------------------------------------------|--------------|
| [figure not shown] | Clinical trial Protocol for ZYH1 – Phase II
ZYH1.09.003.01.PROT

DCGI Submission | Confidential |
|----------------------------------------------------------------------------------|-------------------------------------------------------------------------------------------|--------------|

review by the sponsor's clinical trial monitor and inspection by health authorities (e.g., FDA, DCGI, etc.). The CRA/on-site monitor may review all case report forms, and written informed consents. The accuracy of the data will be verified by reviewing the documents described in Section 8.2.4.

All the ECG's taken at the centre will be photocopied and provided to the sponsor.

### 8.3 QUALITY ASSURANCE AUDIT

A quality assurance audit of this trial may be conducted by the sponsor or sponsor's designees. The quality assurance auditor will have access to all medical records, the investigator's trial related files and correspondence, and the informed consent documentation that is relevant to this clinical trial.

### 8.4 PROCEDURES

#### 8.4.1 Adverse Events

All adverse events occurring during the course of the clinical trial (i.e., from signing the informed consent onwards) will be collected, documented and reported to the sponsor by the investigator according to the specific definitions and instructions detailed in the "Adverse Event Reporting" section of the Investigator Site Master File.

An adverse event is defined as any untoward medical occurrence in a clinical investigation subject administered a pharmaceutical product and which does not necessarily have to have a causal relationship with this treatment.

A serious adverse event is defined as any adverse event which results in death, is immediately life-threatening, results in persistent or significant disability / incapacity, requires or prolongs subject hospitalisation, is a congenital anomaly / birth defect, is to be deemed serious for any other reason representing a significant hazard, which is comparable to the aforementioned criteria.

All adverse events, serious and non-serious, will be fully documented on the appropriate case report form(s). For each adverse event, the investigator will provide the onset, duration, intensity, treatment required, outcome and action taken with the investigational product. The investigator will determine the relationship of the

|                                                         |                                                 |                                                           |
|---------------------------------------------------------|-------------------------------------------------|-----------------------------------------------------------|
| Prepared by:
[name]
Date: 22.06.2010 | Approved by:
[name]
Date:22.06.2010 | Protocol No. ZYH1.09.003.01 .PROT
Version No.: 1.0 (R) |
|---------------------------------------------------------|-------------------------------------------------|-----------------------------------------------------------|

|                                                                                  |                                                                                           |              |
|----------------------------------------------------------------------------------|-------------------------------------------------------------------------------------------|--------------|
| [figure not shown] | Clinical trial Protocol for ZYH1 – Phase II
ZYH1.09.003.01.PROT

DCGI Submission | Confidential |
|----------------------------------------------------------------------------------|-------------------------------------------------------------------------------------------|--------------|

investigational product to all adverse events as defined in the “Adverse Event Reporting” Section of the Investigator Site Master File.

The investigator has the responsibility to report adverse events occurring in a period after a subject completes the trial, as defined and described in the “Adverse Event Reporting” section of the Investigator Site Master File.

#### **8.4.2 Emergency procedures**

Any serious or significant adverse event, whether or not considered related to the investigational product, and whether or not the investigational product has been administered, must be reported immediately by telephone / fax to the sponsor. Details regarding this reporting procedure are provided in the Investigator Site Master File.

Following all such telephone / fax reports the Clinical Monitor must provide a written report of the adverse event and any sequel to the Drug Safety Officer of the sponsor according to the appropriate SOP. These narratives, which confirm the information collected by telephone and may give additional information not available at the time of the initial report.

#### **8.4.3 Pregnancy**

At screening every female subject will be investigated for urine pregnancy test. Women should not become pregnant during the trial and for at least 1 month after the end of the trial period. Adequate contraceptive measures should be taken to prevent pregnancy. Even when contraceptive methods are used, there is a small risk that pregnancy might occur. In case a subject becomes pregnant, then she will be withdrawn from the trial.

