### 3.4 WITHDRAWAL CRITERIA

The investigator may withdraw a subject from the study for any of the following:

- Subject who reports serious AEs (SAE)
- Subject who develops any serious/severe diseases which requires admission in intensive care unit (ICU) or interventional surgery, even if it is not related with investigational drugs
- Any subject found to have entered the study in violation of this protocol or if the subject is uncooperative during the study.
- Any subject who interrupts the study medication for longer than 4 consecutive days.

|                                                         |                                                 |                                                           |
|---------------------------------------------------------|-------------------------------------------------|-----------------------------------------------------------|
| Prepared by:
[name]
Date: 22.06.2010 | Approved by:
[name]
Date:22.06.2010 | Protocol No. ZYH1.09.003.01 .PROT
Version No.: 1.0 (R) |
|---------------------------------------------------------|-------------------------------------------------|-----------------------------------------------------------|

|                                                                                  |                                                                                           |              |
|----------------------------------------------------------------------------------|-------------------------------------------------------------------------------------------|--------------|
| [figure not shown] | Clinical trial Protocol for ZYH1 – Phase II
ZYH1.09.003.01.PROT

DCGI Submission | Confidential |
|----------------------------------------------------------------------------------|-------------------------------------------------------------------------------------------|--------------|

- If it is felt in Investigator's / Medical Expert's opinion that it is not in the subject's best interest to continue.
- In case a subject becomes pregnant, then she will be withdrawn from the trial.
- Subject who do not report to the clinic on +/- 4 days as per the visit schedule.
- Subject's lack of compliance to the study protocol
- Any subject who requires the use of an unacceptable concomitant medication.
- Any subject who wishes to withdraw his / her consent for participation in the study.

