## 4. TREATMENTS

ZYH1 4mg will be administered in hypertriglyceridemic patients with HIV associated lipodystrophy, once daily in the morning before breakfast, for a period of 12 weeks.

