## 4) Visit 4 [Week 12]

- Subjects will be clinically examined and safety and efficacy parameters will be assessed as per Table 1.
- Empty strips will be collected back by the investigators for compliance check.

Unscheduled visits are allowed any time during the study for any untoward effect. Such visits will be recorded in the case record forms (CRFs).

If further investigations are required in case of any AE, investigator will assess the AE and take necessary action, if required. Subjects will be advised to contact the investigator for any complaints within the next two weeks.

During the above period, if any subject misses the drug administration up to 3 days, it will not be considered drop-out or protocol deviation.

During the 12 week program, a designated person from the centre will preferably interview the subject for his/her general health, telephonically.

|                                                         |                                                 |                                                           |
|---------------------------------------------------------|-------------------------------------------------|-----------------------------------------------------------|
| Prepared by:
[name]
Date: 22.06.2010 | Approved by:
[name]
Date:22.06.2010 | Protocol No. ZYH1.09.003.01 .PROT
Version No.: 1.0 (R) |
|---------------------------------------------------------|-------------------------------------------------|-----------------------------------------------------------|

|                                                                                  |                                                                                           |              |
|----------------------------------------------------------------------------------|-------------------------------------------------------------------------------------------|--------------|
| [figure not shown] | Clinical trial Protocol for ZYH1 – Phase II
ZYH1.09.003.01.PROT

DCGI Submission | Confidential |
|----------------------------------------------------------------------------------|-------------------------------------------------------------------------------------------|--------------|

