| Efficacy studies:
Laboratory:
1. Triglyceride
2. LDL
3. VLDL
4. HDL
5. Total cholesterol
6. Non HDL Cholesterol
7. Apo(a)
8. Apo B
9. Fasting insulin and C-peptide for HOMA beta & IR | ✓                                                    |                     | ✓                   | ✓                    |
| Laboratory studies(safety)
1. CBC
2. LFT
3. RFT
4. CPK                                                                                                                                                   | ✓                                                    | ✓                   | ✓                   | ✓                    |
| ECG                                                                                                                                                                                                                  | ✓                                                    |                     |                     | ✓                    |
| Pregnancy test for female subjects (advise for contraception)                                                                                                                                                        | ✓                                                    |                     |                     |                      |
| Dispensing of Study Medication                                                                                                                                                                                       | ✓                                                    | ✓                   | ✓                   |                      |
| Study Medication Tablet Count                                                                                                                                                                                        |                                                      | ✓                   | ✓                   | ✓                    |
| Recording of Adverse Events                                                                                                                                                                                          |                                                      | ✓                   | ✓                   | ✓                    |

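### Section 8.4.3 rules out pregnancy for about 16 weeks and withdraws any subject who becomes pregnant, but Table 1 tests once, at Visit 1, and no pregnancy follow-up is stated

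*Protocol*

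**What the plan says.** Four parts of the protocol bear on this point.

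- **Avoidance period.** Section 8.4.3: "Women should not become pregnant during the trial and for at least 1 month after the end of the trial period". The same section concedes: "Even when contraceptive methods are used, there is a small risk that pregnancy might occur".
- **Testing.** Section 8.4.3: "At screening every female subject will be investigated for urine pregnancy test". In both copies of Table 1 (Protocol Summary and section 6.3), the row "Pregnancy test for female subjects (advise for contraception)" is ticked at Visit 1 and blank at Weeks 2, 6 and 12.
- **Action.** Section 3.4, repeated in section 8.4.3: "In case a subject becomes pregnant, then she will be withdrawn from the trial". The CRF then records when and why she was withdrawn. The withdrawal list in the Protocol Summary does not mention pregnancy.
- **Exposure and outcome.** Section 4 gives the drug "once daily in the morning before breakfast, for a period of 12 weeks". Section 8.4.1 counts an event as serious if, among other criteria, it "is a congenital anomaly / birth defect".

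**The concern.** The withdrawal rule works only if a pregnancy is found. The only scheduled means of finding one is used at Visit 1, when the first supply of drug is handed out. The period that the protocol itself wants free of pregnancy then runs for about 16 weeks.

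If the schedule is followed to the letter, a woman who conceives around or after Visit 1 can be given further drug at Week 2 and again at Week 6 without any check directed at pregnancy. Safety is part of the primary objective (section 2.1). A final report of no exposed pregnancies would carry little information if the only planned test preceded the exposure.

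The birth-defect criterion in section 8.4.1 raises a second problem. A pregnancy that begins in this period would deliver months after the last visit, and the protocol describes no follow-up through which that outcome would reach the sponsor.

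**Working it through.** The plan gives no figure of its own on this point, so there is none to reproduce. The check is day arithmetic and a comparison of sections.

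**Length of the avoidance period**
- Treatment (section 4): 12 × 7 = 84 days.
- Minimum further period (section 8.4.3): 1 month = 28 to 31 days.
- Total: 84 + 28 = 112 days to 84 + 31 = 115 days, or 16.0 to 16.4 weeks.
- Share after the last scheduled visit: 28/112 = 25% to 31/115 = 27%.

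**Coverage by testing**
- Tests scheduled: one, at Visit 1. If Visit 1 falls 0 to 7 days before the first dose (reading its window as Week -1 to 0), the gap from that test to the Week 12 visit is 84 to 91 days, with no test at its end.
- Drug supplied (section 6.3): 2 weeks at Visit 1, 4 weeks at Week 2 and 6 weeks at Week 6, so 14 + 28 + 42 = 84 days. Supply after the only test visit is 28 + 42 = 70 days, and 70/84 = 83%.

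**Other routes to detection**
- Medical history, vital signs and physical examination are ticked at all four visits, and adverse events are recorded at Weeks 2, 6 and 12. None is specified as a pregnancy check.
- The telephone interview on general health is a preference, not a requirement, and is confined to the 12 weeks.
- Section 6.3 adds, under Visit 4: "Subjects will be advised to contact the investigator for any complaints within the next two weeks". On any reading this contact is initiated by the subject and prompted by a complaint. It is not a scheduled contact covering the month after the trial.

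**After withdrawal**
- Section 8.4.3 stops at withdrawal.
- Section 8.4.1 leaves post-trial adverse event reporting to the Investigator Site Master File, and words that duty in terms of subjects who complete the trial. A woman withdrawn for pregnancy has not completed it.
- Pregnancy is not among the listed criteria for a serious adverse event.

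**Scale, on assumptions only.** The documents give neither the number of women able to conceive nor a contraceptive failure rate. Assume n = 10 to 20 of the 50 subjects and an annual failure rate f = 5% to 10%. Expected conceptions over d days are n × (1 − (1 − f)^(d/365)).
- d = 84: 10 × (1 − 0.95^(84/365)) = 0.12 to 20 × (1 − 0.90^(84/365)) = 0.48.
- d = 114 (84 + 30): 0.16 to 0.65.

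The point does not depend on these figures.

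**The case against.** The screening test, the contraception requirement and withdrawal on pregnancy do not contradict one another, and how often to repeat a test in a 12-week study is a design choice. That stands: this is a schedule that does not serve its own rule, not a contradiction. The contraception requirement also runs through the whole period; only the advice is confined to Visit 1.

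Three stronger readings are tempting, and the documents do not support them.

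- **That nobody would look for a pregnancy after Visit 1.** A reader might infer this from the blank cells in Table 1. But history and examination take place at every visit, and a woman who conceived near Visit 1 would be examined at Weeks 2, 6 and 12. A pregnancy may well be noticed; the protocol does not ensure it.
- **That the outcome would go unseen.** Section 8.4.2 requires immediate reporting of serious or otherwise significant adverse events, with a written report that includes their consequences. The Site Master File holds the detailed reporting rules and is not shown, and the consent pages were removed before review. Either could carry a pregnancy rule. What remains is that section 8.4.3 neither states one nor points to one, and that the post-trial clause in section 8.4.1 does not, as worded, reach a withdrawn subject.
- **That post-trial contact is fixed at two weeks, half of the month required.** The two-week sentence closes a paragraph on investigating adverse events, and the next paragraph turns to missed doses in the period just described. It may refer, at least in part, to time on treatment, so no shortfall in days should be computed from it.

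The conception figures are also wholly assumed and cannot carry the case.

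**Conclusion.** The point holds as a cheap improvement. The protocol sets an avoidance period of 112 to 115 days and a withdrawal rule that depends on detection, but schedules one test at its start. The remaining 70 of 84 treatment days are supplied with no further pregnancy check, and the last 25% to 27% of the period has no scheduled contact. A drug-exposed pregnancy can therefore go undetected, and the protocol itself states no reporting or outcome follow-up for one that is found.

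This assumes that the trial period ends at the Week 12 visit and that a month is 28 to 31 days. The part on outcome is conditional, because the Site Master File may already deal with it. The gap in testing is plain from section 8.4.3 and Table 1 and does not depend on that file.

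**What to change.** Reconcile the pregnancy-test and contraception-advice row of Table 1 (both copies) and the end-of-study contact with the avoidance period in section 8.4.3 and the withdrawal rule in sections 3.4 and 8.4.3. The aim is that the rule can be applied across the whole period with the urine test already in use and the visits already planned. Which visits carry a test is for the sponsor to decide. Bring the Protocol Summary's withdrawal list into line at the same time.

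In section 8.4.3, state that a pregnancy is reported to the sponsor and followed to its outcome after withdrawal. If the Site Master File already says so, cross-refer to it there.

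The cost is a protocol amendment, a few urine tests at existing visits and one later contact.
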